#### Main outcome

The main effectiveness outcome will be psychological distress at post-intervention as the primary endpoint, which will be assessed using the short version of the Depression, Anxiety and Stress Scales (DASS-21) (Lovibond and Lovibond, 1996). The DASS-21 is a self-report questionnaire composed of the three negative affectivity subscales of depression, anxiety and stress. Each of the subscales comprises seven items with Likert-type response options (from 0 “did not apply to me at all” to 3 “applied to me very much, or most of the time”). The result of each of these scales will be doubled to achieve equivalence with the long version of 42 items (Lovibond and Lovibond, 1996). The DASS-21 has been specifically validated in the Spanish population, showing strong internal consistency values (total scale *α* = 0.96; depression *α* = 0.93; anxiety *α* = 0.86, and stress *α* = 0.91), as well as appropriate patterns of discriminant, convergent and factorial validity (Daza et al., 2002). The DASS-21 total scale score will be considered the main outcome, and the DASS-21 subscales (i.e., depression, anxiety, and stress) will be considered secondary outcomes. To facilitate interpretation, and following Chin et al. (2019), we will also use a secondary pre-defined binary outcome measure based on the DASS-21 total score that will differentiate those participants who scores 16 points or more to identify individuals with potential anxiety disorders or a major depressive disorder.

#### Secondary outcomes

Burnout symptoms will be evaluated using the Maslach Burnout Inventory Student Survey (MBI-SS) (Schaufeli et al., 2002). This inventory consists of 15 items, in which references to work are changed to references to study. The MBI-SS includes three subscales: exhaustion (5 items), cynicism (4 items) and efficacy (6 items). Participants respond on a Likert-type scale with seven response options ranging from 0 (“never”) to 6 (“always”). The psychometric properties of the MBI-SS Spanish validation have been observed to be adequate (exhaustion *α* = 0.83, cynicism *α* = 0.83 and efficacy *α* = 0.82) (Pérez Fuentes et al., 2020).

Positive affect and negative affect will be evaluated by means of the Positive and Negative Affect Schedule (PANAS) (Watson et al., 1988). This self-report questionnaire consists of two 10-item scales (i.e., positive affect, and negative affect). Each item is scored on a five-point Likert-type scale, from 1 (“not at all”) to 5 (“very much”). The internal consistency of the Spanish version of the PANAS positive and negative scales is adequate, with values of *α* = 0.87 and 0.91, respectively (Sandín et al., 1999).

Emotional regulation will be measured by the Emotional Regulation Questionnaire (ERQ) (Gross and John, 2003). This scale consists of 10 items, to which participants respond using a seven-point Likert scale (1 = “strongly disagree”, 7 = “strongly agree”). The ERQ is designed to measure the tendency of respondents to regulate their emotions through (1) cognitive reappraisal (6 items), and (2) expressive suppression (4 items). The Spanish version of the ERQ shows an adequate internal consistency (cognitive reappraisal: *α* = 0.89–0.90; expressive suppression: *α* = 0.76–0.80), test–retest reliability and convergent/discriminant validity (Cabello et al., 2013).

#### Mechanistic measures

Attachment style will be measured using the Relationship Questionnaire (RQ) (Bartholomew and Horowitz, 1991), a self-report questionnaire in which participants are asked to rate their correspondence to four separate paragraphs, each representing a secure, preoccupied, dismissive or fearful attachment style, by means of a seven-point Likert-type scale. An algorithm allows for a categorical classification of attachment style (i.e., secure, or insecure) (Griffin and Bartholomew, 1994a). The RQ also offers the possibility of measuring two key dimensions underlying attachment in adults: anxiety, which is more self-related, and avoidance, which is more other-related (Griffin and Bartholomew, 1994b). Studies have demonstrated reliability of the RQ questionnaire to be high (Leak and Parsons, 2001). The validated Spanish version of the RQ, which shows adequate psychometric properties (Yárnoz-Yaben and Comino, 2011), will be used in our study.

Experiential avoidance will be assessed with the Acceptance and Action Questionnaire-II (AAQ-II) (Bond et al., 2011). The AAQ-II is a measure of experiential avoidance as an aspect of lack of psychological flexibility. It is made up of seven items on a seven-point Likert-type scale, where 1 is “never true” and 7 is “always true”. The items reflect a lack of willingness to experience unwanted emotions or thoughts, and a lack of ability to be in the present moment and behave according to what is valued when experiencing unwanted psychological events. The instrument presents a unifactorial solution, with good internal consistency (*α* = 0.88), and good convergent, divergent and discriminant validity (Berta-Otero et al., 2022). An adaptation to Spanish will be used (Ruiz et al., 2013).

Compassion will be assessed using the Sussex-Oxford Compassion for Others Scale (SOCS-O) and the Sussex-Oxford Compassion for the Self Scale (SOCS-S) (Gu et al., 2020). The SOCS-O and SOCS-S represent two dimensions, compassion for others and self-compassion, respectively, with 20 items each. Participants indicate how true each statement is using a five-point Likert-type scale, ranging from 1 (“not entirely true for me”) to 5 (“always true for me”). A total score is calculated for the SOCS-O and for the SOCS-S, with higher scores meaning greater levels of compassion for others or self-compassion. The study will use an adaptation of the scale to the Spanish language, which is currently being validated ^1^

Mindfulness skills will be measured with a short version (24 items) of the Five Facets of Mindfulness Questionnaire (FFMQ-SF) (Bohlmeijer et al., 2011). The FFMQ questionnaire is grouped into five mindfulness facets: observing, describing, acting with awareness, non-judging of inner experience, and non-reactivity to inner experience. Participants must indicate the degree to which each of the items is generally true for them on a five-point Likert-type scale, from 1 (“never or very rarely true”) to 5 (“very often or always true”). Scores from the subscales can be combined to produce a total score. The Spanish version of FFMQ-SF presents good internal consistency values for the total score (*α* = 0.70) and subscales (*α* values ranging from 0.65 to 0.80), and an appropriate factorial structure (Cebolla et al., 2012; Asensio-Martínez et al., 2019).

## Data analysis plan

The results will be presented in accordance with CONSORT recommendations (Moher et al., 2001; Moher and Chan, 2014). All the variables will be described and subject to visual inspection at baseline by using frequencies (proportions) for qualitative variables, or means (standard deviations, SD) for quantitative variables.

### Main analysis

The effectiveness of the ABCT group vs. the control group based on relaxation therapy will be evaluated at post-treatment on the main DASS-21 total score, considered as a continuous variable. Multilevel mixed effects linear regressions will be carried out by means of a repeated measures design on an intention-to-treat (ITT) basis, using the restricted maximum likelihood (REML) method. Non-standardised slopes and 95% confidence intervals (95% CIs) for the “group × time” interaction will be provided, together with raw means (SDs) by group. Cohen’s *d* effect size (ES) will be calculated using the combined SD at baseline (Morris, 2008). ESs are considered small when *d* ≤ 0.2; medium when *d* = 0.5; and large when *d* ≥ 0.8 (Cohen, 1988).

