### Sample size

The sample size estimation was calculated based on the assumption that the ABCT group would be able to obtain intermediate effects when compared to the active control condition based on relaxation therapy. In order to determine this, we considered a standardised difference between trial arms on the main outcome (psychological distress, measured by the Depression, Anxiety and Stress Scale (DASS-21) total scale) of 0.5, which is the more conservative estimation observed in a previous similar study that included university students and delivered a third wave psychological intervention based on six meditation sessions (Modrego-Alarcon et al., 2021), and is usually considered a common rule of thumb of clinically significant change (Norman et al., 2003). Considering a power (1-β) of 0.80 for a two-tailed contrast and an α of 0.05 with a group allocation ratio of 1:1, we obtained a group size of approximately 64 subjects. Therefore, the total size of the required sample will be 128 voluntary participants from the university student population. Assuming a loss rate of around 30%, based on a previous similar study (Modrego-Alarcon et al., 2021), we have inflated the numbers so that the total sample size needed will be approximately 190 subjects, 95 in each group.

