### Level of significance

An alpha level of 0.05 will be established using a two-tailed test.

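### The primary group-by-time contrast, read in its ordinary form, is a difference in change from baseline; a baseline-adjusted difference at post-treatment would be more precise at no cost

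*Protocol article*

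**What the plan says.** The Main outcome section fixes the time point: "The main effectiveness outcome will be psychological distress at post-intervention as the primary endpoint". The measure is the DASS-21 total, also collected at baseline and six months.

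The Main analysis section evaluates this outcome at post-treatment with a multilevel linear model for repeated measures, by intention to treat and REML. The effect to be reported is given as: "Non-standardised slopes and 95% confidence intervals (95% CIs) for the “group × time” interaction will be provided". A Cohen's d standardised by the combined baseline SD accompanies it. The section does not mention a baseline covariate or a constraint of equal arm means at baseline, and it does not say how time is coded. The Secondary analysis section extends the same approach to the secondary outcomes and the other time point.

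The Sample size section rests on a single between-arm quantity: "we considered a standardised difference between trial arms on the main outcome", with a value "of 0.5, which is the more conservative estimation observed in a previous similar study". The error rates are given as: "Considering a power (1-β) of 0.80 for a two-tailed contrast and an α of 0.05 with a group allocation ratio of 1:1". The result is stated as "we obtained a group size of approximately 64 subjects", so that "the total size of the required sample will be 128 voluntary participants". No correlation between baseline and post-treatment scores enters the calculation.

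**The concern.** In a repeated-measures model that includes the baseline score as one of the outcomes, with separate arm means at every occasion, the post-treatment group-by-time coefficient is the difference between arms in mean change from baseline. Subtracting the baseline in full carries its noise into the comparison. Adjusting for baseline subtracts only the part that predicts the later score, so it never has the larger variance.

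The loss falls on the primary comparison and, because the same approach is reused, on the continuous secondary outcomes. The sample size was also derived for a plain two-group comparison, so the stated 80% power carries over to the interaction only under a condition on r that the article does not state.

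**Working it through.** **Inputs.** From Sample size: d = 0.5, two-sided alpha 0.05, power 0.80, allocation 1:1, 64 per arm. Assumed, because the article does not give them: the correlation r between baseline and post-treatment DASS-21 total (range 0.3 to 0.7), equal SDs at both times, and d expressed in units of the outcome SD.

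**Step 1: reproduce the plan's figure.** The normal approximation gives n = 2(1.960 + 0.842)² / 0.5² = 62.8, so 63 per arm. The two-sample t-test (noncentral t) needs 64 per arm, with power 0.801. The stated 64 and 128 are therefore reproduced by a plain t-test without any r.

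**Step 2: what the interaction estimates.** One data set was simulated with 64 per arm, three occasions and r = 0.5, and a random-intercept model was fitted by REML with free group, categorical time and interaction. The post-treatment interaction was -0.3219, and the difference in mean change was also -0.3219. With about 30% of follow-up missing, in a second simulated data set, the two were -0.0668 and -0.0677.

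**Step 3: variances, in units of the outcome variance.**
- Difference in change: 2(1 - r)
- Baseline-adjusted difference: 1 - r²
- Ratio, adjusted to change: (1 + r)/2, a reduction of (1 - r)/2
- Change minus adjusted: 2(1 - r) - (1 - r²) = (1 - r)², which is never negative

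In the complete simulated data, constraining the arms to equal baseline means lowered the standard error from 0.159 to 0.138. The squared ratio, (0.138/0.159)² = 0.75, agrees with (1 + 0.5)/2.

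**Step 4: power.** The effective standardised effect is 0.5/√(2(1 - r)) for the interaction and 0.5/√(1 - r²) with adjustment. The last two columns give the evaluable number per arm for 80% power.

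| r | Variance, change | Variance, adjusted | Reduction | Power at 64, interaction | Power at 64, adjusted | n for 80%, interaction | n for 80%, adjusted |
|---|---|---|---|---|---|---|---|
| 0.3 | 1.40 | 0.91 | 35% | 66% | 84% | 89 | 59 |
| 0.4 | 1.20 | 0.84 | 30% | 73% | 87% | 77 | 54 |
| 0.5 | 1.00 | 0.75 | 25% | 80% | 90% | 64 | 49 |
| 0.6 | 0.80 | 0.64 | 20% | 88% | 94% | 52 | 42 |
| 0.7 | 0.60 | 0.51 | 15% | 95% | 98% | 39 | 34 |

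The plain post-treatment t-test has 80% power at every r. The interaction is weaker than that test below r = 0.5, equal at 0.5 and stronger above. The adjusted analysis is stronger throughout the range.

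**The case against.** The strongest reply is that the article does not say the analysis is unadjusted. It does not say that baseline means are free to differ between arms, and a mixed model with arm means constrained equal at baseline also yields a group-by-time coefficient and is baseline-adjusted. Details of that kind are often left to an analysis plan, and none is shown here. This stands in part: the free group term is the natural reading, not a stated fact. But the article does name its primary effect, and that name by default points to the less efficient estimator.

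Four stronger readings are tempting, and the article does not support them.

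- A reader might infer that the baseline is wasted or the estimate biased. Neither follows. The baseline is used as a repeated measure, and the difference in change is unbiased under randomisation. The choice is between two valid estimators.
- A reader might infer that the trial is underpowered. The article gives no r. At r = 0.5 the interaction has the planned power, and above that it has more. The origin of the 0.5 is also not described closely enough to tell whether it was a difference in scores or in change; if it were already in units of the SD of change, 64 per arm would fit the interaction.
- A reader might take the word slopes to mean one linear time trend that mixes post-treatment with six months. Main analysis evaluates the effect at post-treatment, and Secondary analysis treats other time points separately, which points to categorical time. Slope is common usage for a regression coefficient.
- A reader might recompute power from the 140 participants in the abstract. The Sample size section plans about 190, or about 66 per arm after 30% loss (95 × 0.7 = 66.5). The discrepancy between 140 and 190 is a separate matter and does not belong in this comparison.

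**Conclusion.** The point holds as an efficiency improvement, not as an error in the plan. On the ordinary reading of Main analysis, the primary contrast has 2/(1 + r) times the variance of a baseline-adjusted one: 1.54 times at r = 0.3, 1.33 at 0.5 and 1.18 at 0.7. That loss is present for any r below 1, given equal SDs and a free group term. A power shortfall against the planned 80% is conditional: it needs r below 0.5 and d = 0.5 in outcome-SD units, and the article settles neither. With adjustment, 64 per arm exceeds 80% power across the whole range examined, so the trial need not depend on an unstated correlation.

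**What to change.** In Main analysis, name as the primary estimate the baseline-adjusted difference between arms in DASS-21 total at post-treatment, with its 95% CI. Take it from a mixed model with time categorical and either (a) post-treatment and six-month scores as outcomes with baseline DASS-21 as a covariate, or (b) all three occasions as outcomes with arm means constrained equal at baseline. Use the same form for the continuous secondary outcomes. If this is already the intended model, one sentence saying so is enough.

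In Sample size, note that 64 per arm comes from a t-test without baseline adjustment and is conservative for the adjusted analysis, before any allowance for clustering within therapy groups.

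The cost is wording only. The baseline is already collected, and no extra data or participants are needed. The change should be recorded before anyone sees outcome data by arm.

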### Secondary analysis

The effectiveness of the ABCT group vs. the relaxation group regarding the secondary outcomes, as well as secondary time points, will be evaluated following the same analytical strategy used for the main analysis. Per protocol analysis will also be performed, considering only those university student participants who attend at least three sessions (out of six). The clinical significance of improvements between groups will be explored by calculating the absolute risk reduction and number needed to treat (NNT) (and their 95% CI) for the DASS-21 total scores. We will use three criteria for improvement: (i) changing to a less severe cluster in the DASS-21 total score, compared to the one the patient was allocated to at baseline (Chin et al., 2019); (ii) calculating reliable change; and (iii) the clinically significant change of improvements by establishing both reliable change and the cut-off point on the DASS-21 total score, using the Jacobson and Truax method (Jacobson and Truax, 1992).

### Mediation analysis

The potential mediating role of the proposed mechanistic variables will be explored in both the primary and secondary outcomes. For this purpose: (i) primary and secondary outcome pre-follow-up differential scores will be calculated and considered dependent variables; (ii) pre-post differential scores of attachment style, experiential avoidance, compassion (others/self) and mindfulness skills will be calculated and included as potential mediators; and (iii) the group condition (ABCT vs. relaxation therapy) will be considered the independent variable. Indirect effects (IEs) will be estimated using path analyses. Regression coefficients of bootstrapped IEs will be calculated, as well as their 95% CIs based on 10,000 bootstrap samples, considering a significant mediating effect when the mentioned bootstrapped 95% CI does not include zero (Lockhart et al., 2011). The percentage of the mediating effects will also be calculated.

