### Outcomes

Data will be collected using a battery of questionnaires administered at baseline, immediately after the intervention (post-treatment) and at six-month follow-up. Outcomes of the ABCT and the control conditions will be evaluated and compared. The primary outcome will be a self-reported global measure of psychological distress to provide data on the intervention. Secondary outcomes will allow a more detailed exploration of ABCT in terms of depression, anxiety, stress, burnout, emotional regulation and affectivity. Furthermore, the role of attachment style, experiential avoidance, compassion (for others/oneself) and mindfulness skills as potential mediators of outcome will be explored. A breakdown of the study outcomes is given in Table 3.

**Table 3 tab3:** Study outcomes.

Instrument	Assessment area	Kind of outcome	Time
Bespoke survey	Sociodemographic	Characteristics of participants	Baseline
DASS-21	Psychological distress	Primary (total score) Secondary (sub-scales) outcome	Baseline, post-treatment and 6-month follow-up
PANAS	Positive and negative affect	Secondary outcome	Baseline, post-treatment and 6-month follow-up
ERQ	Emotional regulation	Secondary outcome	Baseline, post-treatment and 6-month follow-up
MBI-SS	Burnout	Secondary outcome	Baseline, post-treatment and 6-month follow-up
RQ	Attachment style	Mechanistic measures	Baseline, post-treatment and 6-month follow-up
AAQ-II	Experiential avoidance	Mechanistic measures	Baseline, post-treatment and 6-month follow-up
SOCS-O	Compassion for others	Mechanistic measures	Baseline, post-treatment and 6-month follow-up
SOCS-S	Compassion for the self	Mechanistic measures	Baseline, post-treatment and 6-month follow-up
FFMQ-SF	Mindfulness	Mechanistic measures	Baseline, post-treatment and 6-month follow-up

DASS-21, depression, anxiety and stress scales, 21 items; PANAS, positive and negative affect schedule; ERQ, emotional regulation questionnaire; MBI-SS, Maslach burnout inventory student survey; RQ, relationship questionnaire; AAQ-II, acceptance and action questionnaire-II; SOCS-O, Sussex-Oxford compassion for others scale; SOCS-S, Sussex-Oxford compassion for the self scale; FFMQ-SF, Five facet mindfulness questionnaire short-form.

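### The mediation model relates two change scores taken from the same baseline survey without baseline covariates; if ABCT shifts a mediator, this can produce false significant mediation

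*Protocol article*

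**What the plan says.** The Mediation analysis section of the protocol article fixes three things.

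- Dependent variables: "primary and secondary outcome pre-follow-up differential scores will be calculated and considered dependent variables".
- Mediators: "pre-post differential scores of attachment style, experiential avoidance, compassion (others/self) and mindfulness skills will be calculated and included as potential mediators".
- Decision rule, with group as the independent variable and 10,000 bootstrap samples: "considering a significant mediating effect when the mentioned bootstrapped 95% CI does not include zero".

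The scope is wide: "The potential mediating role of the proposed mechanistic variables will be explored in both the primary and secondary outcomes". The Outcomes section places all instruments in one battery: "Data will be collected using a battery of questionnaires administered at baseline, immediately after the intervention (post-treatment) and at six-month follow-up". No baseline mediator or baseline outcome appears as a covariate in the path equations. Mediation is also secondary hypothesis (c) under Objectives and hypotheses.

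**The concern.** Randomisation protects the path from group to mediator. It does not protect the path from mediator to outcome, which compares participants within arms. In the planned model that path is the regression of one change on another, and both changes subtract values recorded on the same occasion. A student who has a bad week at baseline may score badly on both distress and self-compassion, then drift back on both. The two changes move together without one having caused the other.

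The mechanism question is a stated hypothesis, and the Discussion counts the ability to run mediation analyses among the design's strengths. The Background says that attachment style and compassion for others have not been evaluated before as mechanisms of ABCT. A false positive on either would therefore be the first evidence on the point. The planned percentage mediated would carry the same bias.

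**Working it through.** The article gives no figure for the mediation analysis, so there is none to reproduce. The sample size used below follows its Sample size section: d = 0.5, 80% power and two-sided 5% give 63.8 by the t-test, so 64 per arm and 128 in all, as stated. Taking 70% of 190 gives 133, or 132 in equal arms.

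**Assumed inputs** (not in the article): stability, baseline correlation, and a 0.5 SD shift in the mediator. All scores have variance 1 within arm, and the true mediator-to-outcome effect is zero.

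**Where the false path comes from.** Write M0, M1 for the mediator at baseline and post-treatment, and Y0, Y2 for the outcome at baseline and follow-up. Within arm:

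cov(M1 - M0, Y2 - Y0) = cov(M1,Y2) - cov(M1,Y0) - cov(M0,Y2) + cov(M0,Y0)

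Only the last term is a same-occasion covariance. If it exceeds what the other three cancel, the changes correlate.

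**Model A, autoregressive.** M1 = s·M0 + a·group + error, Y2 = s·Y0 + error, corr(M0,Y0) = r.

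- Covariance of changes: s²r - sr - sr + r = (1-s)²r
- Variance of mediator change: (1-s)² + (1-s²) = 2(1-s)
- False path: b = (1-s)r/2. False indirect effect: a × b.

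At s = 0.5, a = 0.5:

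| r | b | a × b (SD) | False mediation, change scores |
|---|---|---|---|
| -0.3 | -0.075 | -0.0375 | 10% |
| -0.5 | -0.125 | -0.0625 | 23% |
| -0.6 | -0.150 | -0.0750 | 33% |

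The rates come from 800 simulated trials per setting, 132 completers and 600 percentile bootstraps. The simulated b at r = -0.5 was -0.12. With both baselines as covariates the rate was 4% to 6%. If the total effect at six months were 0.5 SD (assumed), the false share mediated at r = -0.5 would be 0.0625/0.5 = 12.5%.

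At s = 0.6 and n = 128, absolute correlations of 0.3, 0.5 and 0.7 gave 9.5%, 17.5% and 30.4% with change scores, against 5.0%, 6.5% and 4.2% adjusted. At s = 0.8 and r = 0.5, the change-score rate falls to 7.8%. At r = 0 it is 4.8%.

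**No shift in the mediator (a = 0).** The mean indirect effect is zero and the change-score rate is 1.0% in Model A (s = 0.6, r = 0.5).

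**Model B, stable trait plus occasion state.** The trait share of variance is 0.6, traits correlate 0.5 and same-occasion states correlate u (magnitudes; sign depends on scoring). Each of the four covariances contains 0.6 × 0.5 = 0.30, which cancels. What remains is 0.4u, over a change variance of 2 × 0.4 = 0.8, so b = u/2. With n = 128 and a = 0.5:

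| u | b | Change scores | Baseline-adjusted |
|---|---|---|---|
| 0 | 0 | 5.0% | 14.8% |
| 0.3 | 0.15 | 36.5% | 36.8% |
| 0.5 | 0.25 | 73.8% | 55.5% |
| 0.7 | 0.35 | 87.7% | 72.5% |

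With a = 0 and u = 0.5 the change-score rate is 5.3%.

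**Requiring both intervals to exclude zero.** A claim must then pass the planned test as well as a second one, so the false rate cannot exceed the smaller entry in each row: at most 5.0%, 36.5%, 55.5% and 72.5%. It never exceeds that of the planned model, but it does not restore 5% when states correlate.

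**Number of indirect effects.** Outcomes: DASS-21 total and 3 subscales (4), MBI-SS 3, PANAS 2, ERQ 2, so 11. Mediators: 5, or 6 with two attachment dimensions. 11 × 5 = 55; 11 × 6 = 66.

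**The case against.** The best defence is that change scores have a real merit. They remove stable differences between people that affect both mediator and outcome. Model B with u = 0 shows this: the planned analysis holds 5.0% and the adjusted one gives 14.8%. The plan also measures mediator change before outcome change, which is good practice. This part stands, and it rules out simply swapping one model for the other.

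It can also be said that the aim is described as exploratory and that multiplicity rules may sit in an analysis plan not shown. That stands for multiplicity: the lack of a Holm or false-discovery rule is not a finding here. It does not cover the model, which the article specifies together with a rule for calling mediation significant.

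Four stronger readings are tempting, and the document does not support them.

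- *The design creates indirect effects wherever none exist.* It needs a shifted mediator and excess same-occasion correlation. The article reports neither, although ABCT is designed to move these constructs.
- *About 55 × 0.05 = 2.75 further false findings come on top.* The simulated rates already include each interval's nominal error. The tests share five group-to-mediator paths, and product tests are conservative when both paths are null. With no mediator shifted, the simulated chance of any false finding among 55 was 9% to 19%, using a joint-significance test in place of the bootstrap.
- *Unreliable change scores make it worse.* Alpha 0.70 for the FFMQ-SF total and an assumed pre-post correlation of 0.5 give (0.70 - 0.50)/(1 - 0.50) = 0.40. The same formula gives 0.76 for the AAQ-II (alpha 0.88) and 0.92 for the DASS-21 total (alpha 0.96). Independent measurement error weakens a true path and does not explain false positives.
- *Baseline adjustment cures it.* It does in Model A, but not in Model B.

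**Conclusion.** The concern holds in conditional form. The planned model can report mediation by a mediator that has no effect on the outcome, provided that ABCT shifts the mediator and that mediator and outcome correlate more within the baseline occasion than across occasions. Under autoregressive scores with stability 0.5, a 0.5 SD shift and baseline correlations of -0.3 to -0.6, the false rate is about 10% to 33% instead of 5%. It is smaller with higher stability, and can be much larger where occasion-specific states correlate. It is not inflated if the mediator is unmoved. These rates illustrate the risk and are not estimates for this trial, because the article gives no correlations or stabilities. The primary analysis and the other group comparisons are unaffected. The change is worth making because a stated hypothesis depends on the model.

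**What to change.** In the Mediation analysis section:

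1. Use the post-treatment mediator and the six-month outcome, with baseline mediator and baseline outcome as covariates in both path equations. Keep the bootstrap.
2. Report the planned change-score model alongside, and claim mediation only where both intervals exclude zero.
3. Add a sensitivity analysis for mediator-outcome confounding, since agreement of the two models does not guarantee 5%.
4. Optionally, name the DASS-21 total at six months as the main mediation outcome and treat the remaining indirect effects (at least 55 in all if every subscale is analysed) as exploratory.

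No new data are needed. The cost is some extra analysis and fewer mediation claims, including some loss of power for true mediators, because a claim must pass two tests.
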